### Objectives

#### Primary Research Question and Hypotheses

The main objective of this study is to investigate if the intervention—the integration of a psychotherapist in a vocational integration program—facilitates access to the labor market for mentally burdened emerging adults by increasing their work ability and mental health literacy and by improving their mental health.

##### Main Hypothesis

Work ability increases significantly from *t*_0_ to *t*_2_.

##### Secondary Hypotheses

Mental health literacy increases significantly from *t*_0_ to *t*_2_. Mental health increases from *t*_0_ to *t*_2_.

Another objective of this study is to determine the feasibility of the intervention and whether it is possible to conduct a clinical trial with unemployed emerging adults who are facing numerous challenges in their transition to adulthood. This study aims to identify implementation difficulties and establish procedures for a potential large-scale trial, including the recruitment of a control group receiving treatment as usual.

The aims are to evaluate the feasibility of the recruitment process and study uptake. Furthermore, we analyze the acceptability and credibility of the therapeutic concept in a non-clinical setting among professionals in vocational training and the emerging adults in these programs.

## Materials and Methods

### Study Design

This is a single-center naturalistic study involving a repeated measure design with three assessments (pre-intervention, post-intervention, and 6-month follow-up). Six month is a common time period for follow up assessments. It allows to collect meaningful data and the risk for ‘lost to follow up’ is reduced compared to longer time periods.

### Recruitment

Participants entering the vocational integration program aged 16–29 years will be recruited for the study by their vocational integration program coach and provided with initial information on the ongoing study. If they agree to participate in the study, the coach will arrange a meeting between the participant and the researcher. Prior to enrollment, all participants are required to read the study information and sign a consent form. Participants will then complete a pre-intervention questionnaire; completion of the questionnaires will take 20–40 min. The researcher, who is a trained psychologist, conducts the clinical interview (duration 45–90 min). The goal of the interview is to obtain a detailed assessment of the participants’ psychopathology; the data will be used only in the descriptive analysis. This first assessment takes place in the first few weeks after the participants have entered the vocational integration program. Alongside the vocational integration program, the participants then take part in the intervention designed for this study.

When the participants leave the vocational integration program and therefore end the intervention, they will complete a post-intervention questionnaire. To ensure data collection, this second assessment will be arranged by the program coach or the researcher. For the 6-month follow-up, the researcher will be responsible for setting up an appointment with the participant. This study was approved by the Ethics Committee of the Canton of Zurich (reference number KEK-ZH-Nr.2017-00936) on September 12, 2017, and is registered with ClinicalTrials.gov (NCT03328286). Duration of the study is 18 months.

#### Participants

To be eligible for the study, participants must be aged 16–29, must take part in the vocational training program, and must be able to understand and complete the questionnaires and understand the clinical interview and the program content in German. Although emerging adulthood is defined as the period from age 18 to 29 (Arnett, 2014), we decided to include 16- and 17-year-olds, as we wanted to avoid excluding a minority and therefore jeopardizing acceptance of the intervention. We foresee that only few participants will not have reached legal age when entering the program.

Coaches in the vocational integration program will verify eligibility.

### Description of the Intervention

The intervention consists in placing a psychotherapist in an already existing vocational integration program. The therapist will hold group sessions once a week lasting 90 min and use well-established group psychotherapy techniques, such as cohesion (Yalom, 1995), empathy (Rogers, 1980), and therapeutic alliance (Bordin, 1979).

The group sessions will provide a social space to discuss challenges, problems, and burdening issues. The group meetings will use elements of Positive Peer Culture programs (Brendtro et al., 2007). The emerging adults can discuss their problems, seek solutions, and help others solve their problems. The issues are prioritized by the group. The aim is to develop a peer culture in which the participants support each other and take responsibility for each other, so that they can experience appreciation and self-efficacy. In the group sessions, the participants can try out new roles and strengthen their self- and external perception and be supported in their identity development. Depending on the psychological distress of the participants, psychology education topics can also be discussed. The psychotherapist can further develop and adapt the contents of the group sessions to the group. The participants have a high degree of co-determination regarding choice of the topics and contents worked on in the group.

Before and after the group psychotherapy, the therapist is on site to support the participants in case of any emergencies (e.g., suicidal thoughts) triggered by the group psychotherapy. The remaining time that the therapist is present in the vocational integration program can be used for individual consultations. We assume that individual consultations will be rare at the beginning and then increase over time. The therapist’s task is to provide support for the emerging adults. If psychotherapy is indicated, the therapist in our study will help the emerging adult to find a therapist outside the vocational integration program. The therapist in the study will provide support during this transition and ensure that a new therapeutic alliance can be built with the therapist outside the program. Since a therapeutic alliance cannot be forced, if the transition cannot be completed successfully, the therapist will look for new solution with the study participant. Study participants can leave the group psychotherapy and the study at any time with no further explanation required and still continue to take part in the vocational integration program.

### Measures

To evaluate the effectiveness of the intervention, the participants will complete the outcome measures described in the following—most of them self-report scales—at pre-intervention, post-intervention, and 6-month follow-up assessment. Table 1 shows the questionnaires as well as their measurement time point within the study. Before data analysis, the questionnaires will be checked for reliability. If reliability values provide unsatisfactory results, we will perform an analysis of the single items.

**Table 1 tab1:** Diagnostic instruments and assessment schedule.

		*t*_0_	*t*_1_	*t*_2_
Mental health	Munich-Composite International Diagnostic Interview (M-CIDI)	x		
	*Allgemeine Depressions-Skala* (ADS)	x	x	x
	Brief Symptom Inventory (BSI)	x	x	x
Mental health literacy	Perceived Stress Questionnaire (PSQ)	x	x	x
	Mental Health Literacy Scale (MHLS)	x	x	x
	General Help-Seeking Questionnaire (GHSQ)	x	x	x
Work ability	Work Ability Index (WAI)	x	x	x
	*Allgemeine Selbstwirksamkeitserwartung* (SWE)	x	x	x
	Rosenberg Self-Esteem Scale (RSES)	x	x	x

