#### Work Ability Index

The WAI measures perceived work ability by a questionnaire-based index (Tuomi et al., 2001). The index is determined based on answers to the following seven items: (1) subjective estimation of current work ability compared with lifetime best; (2) subjective work ability in relation to both physical and mental demands of the job; (3) number of diagnosed diseases; (4) subjective estimation of work impairment due to diseases; (5) sickness absenteeism during the past year; (6) own prognosis of work ability 2 years from now; and (7) psychological resources. The final index score ranges from 7 to 49 and is divided into four work ability ratings: poor, moderate, good, and excellent. In their review article, Radkiewicz et al. (2005) report internal consistencies between 0.54 (Slovakia) and 0.79 (Finland) as part of the NEXT study, with over 38,000 study participants in 10 European countries. This is in line with the results of the German version of Martus et al. (2010), where Cronbach’s alphas ranged from 0.58 to 0.77.

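### The reliability rule lets the trial's own data decide whether the main hypothesis is tested on the Work Ability Index or on its single items

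*Protocol article*

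**What the plan says.** The Measures section sets a two-step rule for all questionnaires. First, "Before data analysis, the questionnaires will be checked for reliability". Then: "If reliability values provide unsatisfactory results, we will perform an analysis of the single items". The article does not say whether the item analysis comes beside the scale score or in its place.

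The main hypothesis is that "Work ability increases significantly from" baseline to the 6-month follow-up. Table 1 lists three instruments under work ability: the WAI, the self-efficacy scale and the Rosenberg scale. The Introduction presents the WAI as the usual measure of work ability and the other two as additions for a fuller picture.

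On the WAI the article says "The index is determined based on answers to the following seven items", and "The final index score ranges from 7 to 49". It cites internal consistencies of 0.54 to 0.79 across ten European countries, and for the German version a study "where Cronbach’s alphas ranged from 0.58 to 0.77".

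The Analysis section sets a 5% significance level and promises an alpha adjustment, with no method or set of tests named. The sample size rests on one repeated-measures F-test at 0.05.

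**The concern.** This is a rule that the article states, not a detail that it leaves open. As written, the variable behind the main hypothesis is settled only once the trial data have been checked for reliability. The WAI is the measure most likely to be affected, because the values cited for it are modest.

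Alpha is also a poor trigger for this index. Its seven items cover different things: current ability, ability in relation to demands, number of diseases, impairment, absence, outlook and psychological resources. Such a mix is expected to give a modest alpha, and a low value does not show that the index has failed.

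At stake is whether the main hypothesis keeps one pre-defined test. If items stand in for the index, up to seven tests take its place, none of them named in advance. The result is either a raised false-positive rate or a loss of power, depending on how far the alpha adjustment reaches.

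**Working it through.** **Inputs from the article:** 7 WAI items; cited alphas 0.54 to 0.79 and 0.58 to 0.77; N = 43 before dropout and 52 in total; three assessments; f = 0.25; α = 0.05; power 0.95. The lowest alpha that the article itself calls satisfying is 0.70, in the Brief Symptom Inventory section.

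**Assumptions, not in the article:** the reliability cut-off (0.70, varied from 0.60 to 0.80); a within-subject correlation of 0.5; normal, equally correlated items.

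**1. The plan's sample size.** For a within factor with m = 3, λ = N·m·f²/(1 − ρ) = 43 × 3 × 0.0625 / 0.5 = 16.1, with 2 and 84 degrees of freedom. Power is 0.951, and 43 is the smallest N that reaches 0.95. The stated N is reproduced for one test at 0.05.

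**2. Chance that sample alpha falls below a cut-off c.** By Feldt's result, (1 − α_true)/(1 − α_sample) follows F with n − 1 and (n − 1)(k − 1) degrees of freedom. For n = 43 and k = 7 these are 42 and 252. The chance is P(F < (1 − α_true)/(1 − c)). For c = 0.70:

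| True alpha | (1 − α_true)/0.30 | n = 43 | n = 52 |
|---|---|---|---|
| 0.54 | 1.533 | 0.975 | 0.984 |
| 0.58 | 1.400 | 0.938 | 0.954 |
| 0.65 | 1.167 | 0.764 | 0.783 |
| 0.70 | 1.000 | 0.522 | 0.520 |
| 0.77 | 0.767 | 0.151 | 0.125 |
| 0.79 | 0.700 | 0.082 | 0.061 |

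Averaged evenly over each cited range, by cut-off:

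| Cut-off | 0.54–0.79, n = 43 | 0.58–0.77, n = 43 | 0.54–0.79, n = 52 | 0.58–0.77, n = 52 |
|---|---|---|---|---|
| 0.60 | 0.297 | 0.248 | 0.287 | 0.232 |
| 0.65 | 0.449 | 0.408 | 0.445 | 0.400 |
| 0.70 | 0.627 | 0.611 | 0.629 | 0.614 |
| 0.75 | 0.803 | 0.814 | 0.810 | 0.825 |
| 0.80 | 0.939 | 0.953 | 0.946 | 0.962 |

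**3. Seven item tests, each at 0.05, no adjustment.** If independent: 1 − 0.95⁷ = 0.302. With correlated items, r = α/(k − α(k − 1)):
- alpha 0.54: r = 0.54/3.76 = 0.144
- alpha 0.79: r = 0.79/2.26 = 0.350

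Simulating seven correlated two-sided tests with these correlations gives a chance of at least one false positive of 0.294 and 0.261. Counting only false positives in the favourable direction, it is 0.152 and 0.132, against 0.025 for a single two-sided test.

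**4. Seven item tests with Bonferroni.** The level per item is 0.05/7 = 0.0071. With f = 0.25, N = 43 and ρ = 0.5, power is 0.816 per item. Power of 0.95 would need N = 61. This holds f at 0.25 for each item; a smaller item effect would lower the power further.

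**The case against.** Several arguments against the point have force.

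- **The text does not say that the score is dropped.** A reader might infer that the plan abandons the WAI when alpha is low. The sentence could equally mean a psychometric look at the items, or item results beside the total. This stands. What remains is that no sentence excludes replacement.
- **A switch is not shown to be likely.** The article gives no cut-off for the WAI, and it adopts the index while citing these alphas without calling them unsatisfactory. At 0.60 or 0.65 a switch is less likely than not on average, and the top of the cited range lies above 0.70. This stands: the risk is material, but its size depends on an assumption. The absent cut-off is not itself the fault, since a full plan may hold it.
- **The check does not look at the effect.** Internal consistency does not show the change over time, so the trigger does not itself inflate error. This stands. Any inflation comes from several unnamed items taking the place of one score.
- **Alpha adjustment is promised.** If it covers the items, familywise error stays at or below 5% and the cost is power. This stands, so 26 to 30% is a conditional figure and not the trial's error rate.
- **The WAI total is never named as the sole main outcome, and f = 0.25 is tied to no instrument.** This is correct. Treating the WAI as the index for the main hypothesis is a reading of the Introduction and Table 1. The rule therefore cannot be blamed for detaching the power calculation from an outcome.
- **This is a single-group study with feasibility aims.** That lowers the severity. It does not remove the point, because the article still sets a main hypothesis and a significance test for it.

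**Conclusion.** The point holds at moderate severity. The Measures section makes the analysed outcome conditional on reliability in the trial data, and nothing protects the scale score. For the WAI, with 43 participants and a cut-off of 0.70, the chance of falling short runs from about 97% (true alpha 0.54) to 8% (0.79). The averages are about 61 to 63% at that cut-off and about 23 to 30% at 0.60. These figures rest on the assumed cut-off and equally correlated normal items.

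If items then replace the index, the harm takes one of two forms: a 26 to 30% chance of at least one false positive in either direction without adjustment, or power of about 0.82 per item instead of 0.95 with Bonferroni. The power figures assume a within-subject correlation of 0.5. The documents do not support the stronger claims that the main outcome will be replaced or that the false-positive rate is already inflated.

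**What to change.** Replace the sentence on single items with a statement that:

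- the WAI total (7 to 49) is analysed for the main hypothesis whatever its alpha in the sample;
- the other scales are analysed by their pre-stated totals. For the Mental Health Literacy Scale this is the total of the retained items: 15 of the 35 were left out, so 20 remain and the published 35 to 160 range no longer applies;
- reliability is reported descriptively;
- any item-level results are exploratory, supplement the total and never replace it.

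The cost is one replaced sentence and a definition of the shortened literacy score. No data, participants or assessments change. With the WAI total as the one test of the main hypothesis at 0.05, the planned N = 43 keeps its power of 0.951 on the assumptions in step 1.

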#### Munich-Composite International Diagnostic Interview

For the clinical interview, we chose the M-CIDI (Wittchen et al., 1998), which is the German version of the DIA-X developed by the World Health Organization. It is a module-based and very flexible diagnostic tool that can support the user reliably and efficiently in diagnosing mental disorders according to the ICD-10 and the DSM-IV. However, no personality disorders are detected. The interview is fully structured and can be completed by a patient with help of clinicians or trained non-clinical personnel in about 45–90 min.

#### Allgemeine Depressions-Skala

The ADS (Hautzinger et al., 2012) is the German version of the Center for Epidemiological Studies Depression Scale (CES-D). It is a 20-item self-rating questionnaire used to assess impairment due to depressive symptoms over the past week. It measures emotional, motivational, cognitive, somatic, and also motor and interactional symptoms. Each item asks how often a symptom occurred in the past week; response options range from “not at all” to “a lot.” There are cut-off values and norms that can be used for a categorical or diagnostic categorization. The ADS has good internal consistency with a Cronbach’s alpha of 0.85 (Meyer and Hautzinger, 2001).

#### Brief Symptom Inventory

Symptom severity will be measured using the German translation of the BSI (Franke and Derogatis, 2000), a 53-item self-report inventory that rates physical and psychological symptoms in the past week. It is the brief form of the Derogatis Symptom Check-List-90 Revised (Derogatis and Unger, 2010). The nine subscales of the BSI assess the following symptom dimensions: somatization, obsessive-compulsive, interpersonal sensitivity, depression, anxiety, hostility, phobic anxiety, paranoid ideation, and psychoticism. Respondents rate each item on a 5-point Likert scale ranging from 0 (“not at all”) to 4 (“extremely”). Alpha coefficients for the nine primary BSI symptom dimensions have revealed satisfying degrees of internal consistency ranging from 0.70 to 0.89, with an *α* = 0.96 for the Global Severity Index (GSI). Convergent validity has been established (Geisheim et al., 2002), with the BSI showing high intercorrelations with established clinical ratings scales.

#### Perceived Stress Questionnaire

The PSQ consists of 20 items that describe stress-related experiences (Fliege et al., 2001). Respondents rate the frequency of occurrence of the described experiences on a 4-point scale: almost never, sometimes, often, and usually, coded from 1 (“almost never”) to 4 (“usually”). A PSQ index is computed using the formula: raw score–30/90, yielding a score between 0 (lowest level of perceived stress) and 1 (highest level of perceived stress). Four subscales with five items each can be derived (worries, tension, joy, demands), with internal consistency values of 0.80–0.86 (Cronbach’s alpha).

#### Mental Health Literacy Scale

The MHLS is a 35-item measure of mental health literacy (O’Connor and Casey, 2015). The measure assesses ability to recognize disorders, knowledge of how to seek mental health information, knowledge of risk factors and causes, knowledge of self-treatments, knowledge of professional treatments available, and help-seeking behavior. The MHLS has a minimum score of 35 and a maximum score of 160; higher scores indicate greater mental health literacy. The MHLS has been shown to have good internal consistency, with a Cronbach’s alpha of 0.87 and test-retest reliability of *r* = 0.79 (*p* < 0.001) (O’Connor and Casey, 2015). For this study, the questionnaire was translated into German, and items 1 through 15 were left out, being considered too complicated to be understood by the target population.

#### The General Help-Seeking Questionnaire

The GHSQ asks respondents to indicate their level of intention to seek help from a number of individuals (e.g., intimate partner, friend, mental health care professional, religious leaders) on a 7-point scale ranging from 1 (“extremely unlikely”) to 7 (“extremely likely”) (Wilson et al., 2005). A higher score indicates a higher intention to seek help for mental health problems. The GHSQ has been shown to be significantly correlated to seeking access to counseling (*rs*(218) = 0.17, *p* < 0.05). Additionally, the GHSQ has been shown to have good test-retest reliability (*r* = 0.92) (Wilson et al., 2005).

#### Work Ability Index

The WAI measures perceived work ability by a questionnaire-based index (Tuomi et al., 2001). The index is determined based on answers to the following seven items: (1) subjective estimation of current work ability compared with lifetime best; (2) subjective work ability in relation to both physical and mental demands of the job; (3) number of diagnosed diseases; (4) subjective estimation of work impairment due to diseases; (5) sickness absenteeism during the past year; (6) own prognosis of work ability 2 years from now; and (7) psychological resources. The final index score ranges from 7 to 49 and is divided into four work ability ratings: poor, moderate, good, and excellent. In their review article, Radkiewicz et al. (2005) report internal consistencies between 0.54 (Slovakia) and 0.79 (Finland) as part of the NEXT study, with over 38,000 study participants in 10 European countries. This is in line with the results of the German version of Martus et al. (2010), where Cronbach’s alphas ranged from 0.58 to 0.77.

#### Rosenberg Self-Esteem Scale

Self-esteem will be assessed using the German version of the 10-item Rosenberg Self-Esteem Scale (Ferring and Filipp, 1996). The RSES is well validated and is the most commonly used measure of self-esteem. Several studies with different samples have provided evidence of its reliability and stability (Martín-Albo et al., 2007; Mimura and Griffiths, 2007; Sinclair et al., 2010). Respondents rate the items on a 4-point Likert scale ranging from 0 (“strongly disagree”) to 3 (“strongly agree”). Satisfactory characteristic values were obtained with regard to both internal consistency and split-half reliability. The estimation of internal consistency varies between the samples, with values in the range of 0.81–0.87; reliability of the split-half calculation according to Guttman’s and Spearman’s rules is between 0.82 and 0.84, so that the scale can be described as sufficiently reliable (Ferring and Filipp, 1996).

#### General Self-Efficacy

The GSE is a self-report measure of self-efficacy. The 10-item scale was reduced in 1981 from the original 20-item scale developed by Jerusalem and Schwarzer (1992) and has since been adapted for 28 languages. The response format for the 10 items is four options on a Likert scale ranging from “not at all true” to “exactly true.” Responses to the 10 items are summed to obtain a GSE total score that ranges from 10 to 40. Numerous studies have produced good psychometric parameters for the scale. When comparing 25 nations, the internal consistency for the overall sample was 0.86 and 0.81 for the German sample (Scholz et al., 2002).

